## Abstract

Supplemental Digital Content is available in the text

## Introduction

1

Sepsis is a serious life-threatening inflammatory reaction caused by infection. The pathological process involves multiple organs. The lung is the most vulnerable target organ for sepsis, and ALI/ acute respiratory distress syndrome (ARDS) appears at the earliest and has the highest incidence.^[1]^ Presently, with no definitive treatment, sepsis-induced ARDS is mainly managed by symptomatic and supportive treatment, and its morbidity and mortality are still high. 25% to 50% of patients with severe sepsis are complicated with ALI/ARDS.^[2]^ The development of ALI/ARDS can significantly worsen the prognosis of patients, causing the mortality rate of septic shock in the intensive care unit (ICU) to rise from 11% to 38% with the mortality rate as high as 40% in some patients with ALI/ARDS.^[3]^ Most of the deaths were attributed to sepsis and multiple organ failure and not to primary respiratory failure. Therefore, there is an urgent need to carry out more extensive and in-depth research on the pathogenesis, prevention, and treatment strategies of ARDS.

The functional change of pulmonary vascular endothelial cells is a key link in the pathophysiological process of sepsis-induced ARDS, which plays an important role in microcirculation abnormality, septic shock, and multi-organ dysfunction. Vascular endothelial cells are highly bioactive and participate in the regulation of vascular smooth muscle tone, the exchange of cells and nutrients, the maintenance of blood flow, and the balance of local pro-inflammatory and anti-inflammatory mechanisms.^[4]^ Basic experiments show that inflammation-induced capillary leakage occupies an important position in the pathogenesis of ARDS. Inflammation factor stimulation leads to lung endothelial cell damage or apoptosis, and endothelial barrier damage, leading to an increase in the vascular endothelial permeability and an increase in the liquid infiltration tissue clearance,^[5,6]^ which belongs to the traditional Chinese medicine (TCM) in the category of "water drink syndrome”.

The pathogenesis of the disease is Yang deficiency and water overflowing, which cannot be attributed to the ordinary way, resulting in tissue edema, and kidney yang is the root of the whole body Yang Qi. Therefore, we use the Fusu mixture to treat sepsis-induced ARDS patients, which makes the kidney yang warm and latent in the lower energizer. The Fusu mixture is composed of 6 TCMs, namely, Aconiti Lateralis Radix Praeparata, Carapax Testudinis, Amomi Fructus, Ephedra sinica Stapf, Rhizoma zingiberis, and Radix glycyrrhizae.

TCM has a long history and rich experience in the treatment of infectious diseases. At the early stage, we determined the main components of the Fusu mixture by HPLC and found that the compound contained glycyrrhizin, glycyrrhizic acid, 6-gingerol, and other components. Through animal experiments, it was confirmed that the TCM resuscitation mixture could improve the pathological changes of lung tissue in rats, inhibit the expression of heparanase in the plasma of acute lung injury caused by sepsis, and reduce the release of inflammatory factors. This shows that the Fusu mixture has a certain effect on sepsis-induced ARDS,^[7]^ which provides basic evidence for the clinical treatment of the Fusu mixture.

In the previous clinical practice, we found that the TCM Fusu mixture could supplement the basic treatment of Western medicine, clinically reduce the Extravascular lung water index of patients with sepsis-induced ARDS, and improve the prognosis of patients. ^[8]^ However, more sufficient clinical evidence is needed to confirm this. Therefore, our goal is to conduct a prospective, single-center, single-blind, randomized controlled trial to evaluate the efficacy and safety of Fusu mixture in the treatment of sepsis-induced ARDS. The results of this trial may provide evidence that the Fusu mixture is an effective prescription for sepsis leading to ARDS.

Current studies have shown that miRNA, circRNA, and lncRNA are related to endothelial barrier function, ^[9–18]^ while the regulatory mechanism of the complex regulatory network based on the whole transcriptome on the endothelial function of sepsis has not been reported. Therefore, based on these previous studies, we hypothesize that the Fusu mixture may achieve therapeutic effects by regulating the expression of genes in the whole transcriptome.

## Method and design

2

### Design

2.1

This is a single-center, single-blind, randomized controlled trial involving 620 patients who will be randomly assigned to either the Western medicine treatment group or the integrated Chinese and Western medicine treatment group. Each treatment course is for 7 days, which includes 2 courses of treatment. The clinical efficacy and safety of Fusu mixture for sepsis-induced ARDS patients will be evaluated, and the related mechanisms of action will be discussed based on the whole transcriptome sequencing. This study will adhere to the Standard Protocal Items: Recommendation for Interventional Trials 2013 statement. Refer to Document 1, for the Standard Protocol Items: Recommendations for Interventional Trials checklist.^[19]^ The study flow chart is shown in Figure 1 and the specific timing of the study and the collection of data from baseline to follow-up are shown in Figure 2.

**Figure 1 F1:**
[figure not shown]
Flow chart of the study design. ARDS = acute respiratory distress syndrome, TCM = traditional Chinese medicine.

**Figure 2 F2:**
[figure not shown]
Schedule of enrollment, interventions, assessments, and data collection. CRP = Serum inflammatory index includes, PCT, IL-6, TNF-a; blood gas analysis includes: Lac, PaO2/FiO2; Liver function index monitoring includes: ALT, AST, Tbil, GGT, ALP; Renal function index monitoring includes: Scr, BUN, eGFR. ALP = alkaline phosphatase, ALT = alanine aminotransferase, AST = aspartate aminotransferase, BUN = blood urea nitrogen, CRP = C-reactive protein, eGFR = estimated glomerular filtration rate, GGT = γ-glutamyl-transferase, IL-6 = interleukin-6, Lac = lactic acid, PaO2/FiO2 = oxygenation index, PCT = procalcitonin, Scr = serum creatinine, Tbil = total bilirubin, TNF-α = tumor necrosis factor-alpha.

### Moral certification

2.2

The study was approved after meeting the requirements set by the ethics committee of the affiliated hospital of Chengdu University of TCM (No. 2019KL-049). Following the Declaration of Helsinki (Edinburgh, 2000), this study trial (ChiCTR1900027988) was registered with clinicaltrials.gov on December 7, 2019 (Version. V1.0), and all participating staff was trained in standard operating procedures. If any amendments are made to the agreement, the review and approval of the ethics committee will be sought again.

### Research environment and participants

2.3

All patients with sepsis-induced ARDS admitted to the general and respiratory ICU of the affiliated hospital of Chengdu University of TCM during the study period will be screened and enrolled. Informed consent will be obtained from eligible patients and then they will be randomly divided into the Western medicine treatment group and the integrated Chinese and Western medicine treatment group in a 1:1 ratio. If the patient is unable to give informed consent at the time of admission to ICU due to the severity of ARDS, informed consent will be obtained from the next of kin or from an independent physician. In these cases, we will obtain informed consent from the patient as soon as possible.

### Sample size

2.4

Calculating the sample size was based on the 28-day mortality. According to the available literature, the 28-day mortality of the western medicine treatment group is about 40%, whereas that of the treatment group with integrated traditional Chinese and Western medicine is about 30%. The software Power Analysis and Sample Size version 11.0 (PASS 11.0) was used to calculate the sample size of the 2 groups, assuming that the test level is *α* = 0.05, the probability of making mistakes *β* = 0.2, considering the 10% loss rate, a total of 620 patients will be enrolled.

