#### Primary outcome

3.2.1

The 28-day mortality will be compared between the 2 groups.

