### Statistical analysis

3.6

Before analysis, 2 similar participants with complete data will be carefully examined to ensure that the data is correct. All data analyses will then be based on treatment intention.

The data will be analyzed using the statistical software package SPSS 22.0 (Chicago, IL). The analysis method will be selected according to the distribution characteristics of the data. The measured data will be expressed as the mean ± the standard deviation. First, the normal test and the homogeneity test of variance will be performed. In the case of normal distribution and equal variance, a *t*-test will be performed; otherwise, a nonparametric test will be utilized. The difference will be statistically significant when *P* ≤ .05.

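### The total of 620 matches the stated inputs only under an undeclared one-sided 5% test; a two-sided comparison at P ≤ .05 has about 70–74% power, not 80%

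*Protocol article*

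**What the plan says.** Protocol article, Section 2.4 (Sample size): "Calculating the sample size was based on the 28-day mortality". The assumed 28-day mortality is about 40% with Western medicine and about 30% with the combined treatment. The calculation, done in PASS 11.0, is described as "assuming that the test level is *α* = 0.05" and "the probability of making mistakes *β* = 0.2". It ends with "considering the 10% loss rate, a total of 620 patients will be enrolled". Sections 2.3 and 2.5 give 1:1 allocation.

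Section 3.2.1 (Primary outcome): "The 28-day mortality will be compared between the 2 groups".

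Section 3.6 (Statistical analysis): "The difference will be statistically significant when" P ≤ .05. The same section bases all analyses on intention to treat.

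None of these sections names a direction, a one-sided hypothesis or a one-sided significance level.

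**The concern.** A reader who takes the stated rates, α, β and loss and applies the usual two-sided calculation does not come near 620. The number depends on a choice the article never mentions, and either way of resolving it causes a problem.

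- **If the primary test is two-sided**, the stated type II error is wrong. A mortality reduction of exactly the size the trial was designed to find would be missed about three times in ten. A non-significant result could then be read as coming from a trial with 80% power.
- **If a one-sided 5% test was intended**, the chance of wrongly declaring a mortality benefit for Fusu is 5% in that direction, twice the 2.5% of a two-sided 5% test. The primary test could then never formally declare excess mortality in the Fusu arm.

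While the point stays open, the sidedness could also be chosen after the data are seen.

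**Working it through.** **Inputs (Section 2.4; allocation from Sections 2.3 and 2.5).** p₁ = 0.40, p₂ = 0.30, difference d = 0.10, α = 0.05, power 0.80, loss 10%, allocation 1:1. The mean rate is p̄ = 0.35.

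- p₁(1−p₁) + p₂(1−p₂) = 0.24 + 0.21 = 0.45
- 2p̄(1−p̄) = 2 × 0.35 × 0.65 = 0.455
- z for 80% power = 0.8416; z for one-sided 0.05 = 1.6449; z for two-sided 0.05 = 1.9600

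**Formulas, per arm**

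- Unpooled: n = (z_α + z_β)² × 0.45 / d²
- Pooled: n = [z_α√0.455 + z_β√0.45]² / d²

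**Step 1. Reproduce the plan's figure, one-sided α = 0.05**

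- Unpooled: (1.6449 + 0.8416)² × 0.45 / 0.01 = 6.1826 × 45 = 278.2, so 279 per arm and 558 in total. 558/0.9 = **620** exactly.
- Pooled: 280.3, so 281 per arm and 562 in total. 562/0.9 = 624.4, so 625 (626 with equal arms). With loss added as n × 1.1, 281 × 1.1 = 309.1, so 310 per arm and again **620**.

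**Step 2. Same inputs, two-sided α = 0.05**

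- Unpooled: (1.9600 + 0.8416)² × 45 = 7.8489 × 45 = 353.2, so 354 per arm and 708 in total. 708/0.9 = 786.7, so **787**.
- Pooled: 355.9, so 356 per arm and 712 in total. 712/0.9 = 791.1, so **792**.
- The arcsine formula also gives 356 per arm. Continuity correction raises the pooled figure to 376 per arm (836 enrolled). Time-to-event formulas give about 767 to 790 enrolled.

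The two proportion formulas need 708–712 patients before any loss, already above 620, so no loss convention closes the gap. Against 787–792 the shortfall is 167–172 patients.

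**Step 3. Power that 620 delivers at 40% v 30%**

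Power = Φ[(d − z_α√(0.455/n)) / √(0.45/n)]

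| Evaluable per arm | Two-sided 0.05 | One-sided 0.05 |
|---|---|---|
| 279 (10% lost) | 69.8% | 79.8% |
| 310 (none lost) | 74.3% | 83.4% |

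Worked for 279, two-sided: √(0.455/279) = 0.04038 and √(0.45/279) = 0.04016. (0.10 − 1.9600 × 0.04038)/0.04016 = 0.519, and Φ(0.519) = 0.698. Exact enumeration of the two-sided chi-square test agrees: 69.9% at 279 per arm and 74.3% at 310.

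The two-sided type II error is therefore 1 − 0.743 = 25.7% to 1 − 0.698 = 30.2%, against the stated 20%.

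**Step 4. Effect that 558 evaluable patients can detect, two-sided**

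With 279 per arm and 40% in the control arm, power is 79.7% at 28.8%. About 80% power therefore needs a difference of about 11.2 percentage points rather than 10.

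**The case against.** **The article never says two-sided.** If the test is one-sided, the inputs and 620 agree. A condensed article may also leave sidedness to the full protocol or the SAP, neither of which is shown. This stands in part: two-sided is the ordinary reading of an undirected comparison at P ≤ .05, not a declared fact, so the power figures here are conditional on it. But no unseen document can make 620 yield 80% two-sided power. It could only confirm a one-sided 5% test, which belongs beside the α in Section 2.4.

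**The rates are given only approximately.** Stretching them to 40.49% v 29.51%, the most favourable values that still round to 40% and 30%, gives 292.3 (unpooled) to 295.0 (pooled) per arm. Rounded up, that is 293–296 per arm, and 586/0.9 to 592/0.9 is 652–658 enrolled. The gap narrows but stays open.

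**70% is the less favourable figure.** Under intention to treat with day-28 vital status known for everyone, two-sided power is 74.3%. That is fair, and both figures are given. The lower one uses the plan's own 10% loss.

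**The route to 620 is not established.** Two one-sided routes reach it (Step 1), so the exact formula used is unknown. Both are one-sided. A two-sided calculation at 70% power also comes close (281 per arm, 626 enrolled), but it contradicts β = 0.2 and would confirm the 70% figure.

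**Harm is assessed elsewhere.** Sections 3.3 and 3.4 provide for safety tests and adverse-event reporting. The concern about a one-sided test is therefore limited to excess mortality in the primary comparison.

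**Conclusion.** The concern holds. With the plan's own rates, α, β and 10% loss, 620 corresponds to a one-sided 5% test that the article does not declare. Read as the undirected comparison at P ≤ .05 that Sections 3.2.1 and 3.6 describe, the trial has 69.8% power with 558 evaluable patients and 74.3% with all 620. The stated β of 0.2 is not delivered.

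This assumes true mortality of 40% and 30%, equal arms, a comparison of two proportions without continuity correction, and a two-sided test. If the sponsor did intend a one-sided 5% test, the power claim is right, but the error rate in favour of Fusu is 5% and must be stated. Under a two-sided test at 0.05 the type I error is sound and the trial remains valid; it is the power statement that is wrong.

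**What to change.** Keep 620 and correct the statement.

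- **Sections 2.4 and 3.6:** state that the primary test of 28-day mortality is two-sided at 0.05.
- **Section 2.4:** replace the 80% claim with, for example: *620 patients give about 70% power to detect 40% v 30% with 10% loss, and 74% with complete day-28 vital status; with 10% loss, power is about 80% for 40% v 28.8%.*
- Plan for complete day-28 vital status, which accounts for the difference between 70% and 74%. A prespecified covariate-adjusted analysis may recover more, but the article gives no figures from which to size that gain.

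The cost is rewording in two sections and a less favourable stated power, with no extra patients. It should be done before any outcome comparison by arm is seen.

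If the sponsor is unwilling to accept a 26–30% type II error on mortality, the alternative is to enrol 787–792, that is 167–172 more patients. If a one-sided test was truly intended, it must be declared and justified in both sections, with the 5% one-directional error rate made explicit.

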### Randomization and allocation concealment

2.5

Members of The Sichuan TCM Evidence-Based Medicine center will use SAS 9.2 software (SAS, Cary, NC) to generate 620 random serial numbers. After screening and baseline evaluation, the patients with ARDS will be randomly divided into 1 of the 2 groups. Eligible patients will be assigned to the treatment group of integrated traditional Chinese and Western medicine or the treatment group of Western medicine alone at a proportion of 1:1. The group number will be provided in a carbon-free sealed envelope. The envelope will be kept by the study administrator, who will not be directly involved in any participant's recruitment or follow-up, and the group number will be disclosed later. The administrator will open an envelope and provide participants with their group number on the day of inclusion.

### Diagnostic criteria

2.6

Participants must meet the diagnosis criteria for both sepsis and ARDS. For the diagnosis standard of sepsis, please refer to the “Sepsis3,0 Diagnosis criteria which was published by the American Medical Association in 2016,”^[20]^ and the “2018 emergency treatment guidelines for sepsis/septic shock in China”.^[21]^ For patients with infection or suspected infection, sepsis can be diagnosed when the score of sepsis related sequential organ failure (sofa) is more than or equal to 2 points higher than the baseline. See Table 1 for the scoring criteria of sofa and ARDS Berlin diagnostic criteria are shown in Table 2.^[22]^

**Table 1 T1:**
[figure not shown]
SOFA scoring standard: the dosage of catecholamine isμg/(kg min), the dosage is at least 1 h, and the score range of Glasgow coma scale is 3 to 15 points. The higher the score, the better the neurological function.

**Table 2 T2:**

Western medicine diagnostic criteria for acute respiratory distress syndrome.

### Qualification criteria

2.7

#### Inclusion criteria

2.7.1

Patient must meet all the following criteria:

(1)Patients 18 to 80 years of age.(2)The course of the disease within 12–48 hours, meeting the diagnostic criteria for sepsis and ARDS.(3)Oxygenation index (PaO2/FiO2) ≤200 in ARDS.(4)Patients with mechanical ventilation.(5)In order to conform to the Declaration of Helsinki and Chinese clinical trial research regulations, the patient or family members must know the content of the study and sign informed consent voluntarily.

#### Exclusion criteria

2.7.2

Patients who meet 1 or more of the following exclusion criteria cannot be included:

(1)Pregnant or lactating women.(2)Patients allergic to the drugs used in the trial.(3)Those with indications of surgery.(4)Patients with other serious physical diseases, AIDS, and malignant tumors.(5)Patients who are expected to die or give up an active rescue or refuse conventional supportive treatment in Western medicine within 12 hours of admission to the ICU.(6)Patients with contraindications for femoral artery catheterization, central venous catheter placement, and blood transfusion.(7)Patients with chronic heart failure or end-stage multi-organ failure.(8)Currently participating in other pharmaceutical research.(9)Patients who are employees of the research site or family members of employees at the research site.

### Termination and withdrawal criteria

2.8

All participants will be informed that they have the right to withdraw from the trial and if they do, they will also receive the standard treatment. The reason for withdrawal will be recorded in their case report file (CRF). The criteria for discontinuing treatment and withdrawing patients from the study are:

(1)The experience of adverse events related to taking the drugs, and the researchers determine that it is not appropriate to continue administering the drugs(2)Required treatment for another serious disease during the study(3)Poor compliance or withdrawal midway through the study(4)Inability to tolerate 2 weeks of the intervention and cannot continue the research due to the automatic requirement of discharge or transfer(5)Giving up treatment in advance due to economic burden and/or other factors(6)The experience of a serious adverse event in the process of the trial, such as a life-threatening incident or even death, and the researchers could not continue

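### One list in section 2.8 serves for stopping treatment and for leaving the study, and it names death, so the intention-to-treat comparison of 28-day mortality is not protected

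*Protocol article*

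**What the plan says.** Section 2.8 of the protocol article introduces its list with "The criteria for discontinuing treatment and withdrawing patients from the study are", so the same six criteria end treatment and end participation. In summary they are:

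- (1) drug-related adverse events after which the researchers judge further dosing inappropriate;
- (2) need for treatment of another serious disease;
- (3) poor compliance or withdrawal part-way;
- (4) not tolerating the two weeks, joined with being unable to continue because of discharge or transfer;
- (5) "Giving up treatment in advance due to economic burden and/or other factors";
- (6) "The experience of a serious adverse event in the process of the trial, such as a life-threatening incident or even death", with the added condition that the researchers could not continue.

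For patients who withdraw, the section provides standard treatment and a record of the reason in the case report file.

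Elsewhere, section 3.2.1 gives the primary outcome: "The 28-day mortality will be compared between the 2 groups". Section 3.6 states: "All data analyses will then be based on treatment intention". Section 3.1.2 sets two 7-day courses, so study treatment ends at 14 days. Section 2.4 assumes 28-day mortality of 40% against 30%, allows 10% loss and enrols 620.

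**The concern.** Stopping a study drug and leaving a study are different events. Intention to treat tolerates the first freely, but it needs the outcome of every randomised patient whether or not treatment continued. A single list makes each reason for stopping treatment also a reason for leaving, and one of the listed events is the primary outcome itself.

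Several of the other reasons are prognostic. The patients are mechanically ventilated with an oxygenation index of 200 or below (2.7.1), so a life-threatening event often lies close to the outcome. Exclusion criterion (5) in 2.7.2 already groups patients expected to die with those who abandon active rescue, which suggests that giving up treatment is not neutral either.

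The exits may also differ by arm. Fusu is added to standard care and sections 3.1.1 and 3.1.2 describe no placebo, so criteria (1) and (4) probably arise more often in the Fusu arm. If vital status is lost after such exits, the arms compared at day 28 are no longer the arms that were randomised.

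**Working it through.** **The passages side by side.** Section 2.8 takes patients out of the study for reasons tied to prognosis. Section 3.2.1 needs vital status at day 28, and section 3.6 needs it for everyone randomised. Treatment lasts 14 days, so if day 28 is counted from about the start of treatment, any exit during treatment leaves at least 28 − 14 = 14 days of the outcome window to be followed. No section shown says that this happens.

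**The plan's own figure.** With p1 = 0.40, p2 = 0.30, mean 0.35 and 80% power, n per arm = [z(α)·√(2·0.35·0.65) + 0.842·√(0.40·0.60 + 0.30·0.70)]² / 0.10².

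- One-sided 5% (z = 1.645): 281 per arm; 281 × 1.1 = 309.1, so 310 per arm and 620 in total, as stated.
- Two-sided 5% (z = 1.960): 356 per arm, and 784 to 792 in total after the loss allowance.

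The choice of sides is a separate matter. All that is needed here is 620/2 = 310 per arm and, if loss is equal, a 10% allowance of 31 per arm.

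**Illustration 1: loss in one arm, no true effect.** If a fraction w of an arm is dropped and a share d of those would have died, apparent mortality is (0.40 − w·d)/(1 − w). Both w and d are assumptions.

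| w | d | Calculation | Apparent mortality | Shift from 40% |
|---|---|---|---|---|
| 5% | 80% | 0.36/0.95 | 37.9% | −2.1 points |
| 10% | 80% | 0.32/0.90 | 35.6% | −4.4 points |
| 10% | 100% | 0.30/0.90 | 33.3% | −6.7 points |
| 10% | 0% | 0.40/0.90 | 44.4% | +4.4 points |

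The last row shows that losing survivors reverses the sign.

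**What the 33.3% row would do to the test.** Suppose the loss is in the Fusu arm: 124 of 310 die in the control arm, and (124 − 31)/(310 − 31) = 93/279 in the Fusu arm. The pooled rate is 217/589 = 0.368. The standard error is 0.0398 under the null and 0.0396 under the alternative. The chance that a two-sided 5% test favours Fusu is Φ[(0.0667 − 1.96 × 0.0398)/0.0396] = Φ(−0.29), about 39% instead of 2.5%. This is an extreme case, with every lost patient a death and all in one arm.

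**Illustration 2: loss in both arms, true effect 40% against 30%.** If a share f of deaths is dropped from each arm, the observed rate is p(1 − f)/(1 − p·f). With f = 25%, the control arm shows 0.30/0.90 = 33.3% and the Fusu arm 0.225/0.925 = 24.3%. The difference is 9.0 points instead of 10. Two-sided power by the same normal approximation falls from 74.3% (310 per arm, no loss) to 65.8%.

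**The case against.** The strongest answer is that no passage says outcome collection stops. Withdrawn patients receive standard treatment, section 3.6 commits to intention to treat, and both fit with ascertaining vital status at day 28. The article condenses a fuller protocol, the schedule in Figure 2 is not shown, and follow-up of patients who leave early may be set out there. This stands as far as it goes: a reader might infer that intention to treat is impossible under 2.8, and the text does not support that.

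Four other strong readings also fail.

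- **That deaths are dropped from the count.** A patient who dies by day 28 has a known status, and under 3.6 that is an outcome event. Naming death as a withdrawal reason is bad drafting, not an exclusion rule.
- **That any serious adverse event removes a patient.** Criterion (6) also requires that the researchers could not continue.
- **That recovering patients leave by criterion (4).** That criterion joins intolerance with discharge or transfer, so discharge on recovery is not plainly covered.
- **That criteria (1) and (4) can apply only to the Fusu arm.** This is plausible, but section 3 places both arms under interventions and both arms receive drugs.

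The illustrations are also open to challenge, since the loss shares are invented for the purpose. The equality of the 10% loss allowance and the 10-point effect shows nothing about bias.

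What remains is the stated rule. The point is not that a missing-data method is absent, which belongs to the analysis plan. It is that the protocol withdraws patients from the study for prognostic reasons, and an analysis plan may be unable to recover vital status that was never collected.

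**Conclusion.** The point holds as a badly fixed rule. Read plainly, section 2.8 conflicts with the intention-to-treat commitment in 3.6 and exposes the sole primary outcome to loss related to prognosis and possibly to arm. It fails to protect the comparison; it does not by itself defeat it. If day-28 status is in fact collected for everyone, the remaining fault is one of wording.

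No size can be estimated, because the article gives no withdrawal rates by arm or reason. The shifts calculated above, from 6.7 points down to 4.4 points up in the affected arm, show only what one-sided loss within the planned 10% could do if those patients were left out of the analysis. The direction depends on who is lost and from which arm.

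**What to change.** Split section 2.8 in two.

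- **(a) Reasons to stop study treatment.** Keep the clinical criteria as they are, and state that patients who stop remain in the study and in follow-up.
- **(b) Withdrawal from follow-up.** Limit this to withdrawal of consent to further data collection. Poor compliance, giving up treatment, adverse events, and discharge or transfer then no longer end participation.

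Remove death from the withdrawal list and count it as a primary-outcome event, including when it follows the end of study treatment. Obtain vital status at day 28, by record or telephone, for every randomised patient unless that consent is withdrawn. Analyse all patients as randomised. How to handle any status still unknown can be left to the analysis plan.

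The cost is an amendment, with the ethics review that section 2.2 requires, and a brief vital-status check for patients who leave early. The sample size does not change.
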